## Abstract

**Background:** Snakebites affect over 5 million people each year, and over 100,000 per year die as a result. The only available treatment is antivenom, which has many shortcomings including high cost, intravenous administration, and high risk of adverse events. One of the most abundant and harmful components of viper venoms are the zinc-dependent snake venom metalloproteinases (SVMPs). Unithiol is a chelating agent which is routinely used to treat heavy metal poisoning.
*In vivo* experiments in small animal models have demonstrated that unithiol can prevent local tissue damage and death caused by a certain viper species. This phase I clinical trial will assess the safety of ascending doses of unithiol with a view for repurposing for snakebite indication.

**Methods:** This open label, single agent, phase I clinical trial of a repurposed drug has a primary objective to evaluate the safety of escalating doses of unithiol, and a secondary objective to describe its pharmacokinetics. In total, 64 healthy Kenyan volunteers from Kilifi County will be dosed in consecutive groups of eight, with dose escalation decisions dependent on review of safety data by an independent data safety monitoring board. Four groups will receive ascending single oral doses, two will receive multiple oral doses, and two will receive single intravenous doses. Follow-up will be for 6-months and includes full adverse event reporting. Pharmacokinetic analysis will define the Cmax, Tmax, half-life and renal elimination.

**Conclusions:** This clinical trial will assess the safety and tolerability of a promising oral therapeutic in a relevant setting where snakebites are prevalent. Unithiol is likely to be safer than antivenom, is easier to manufacture, has activity against diverse snake species, and can be administered orally, and thus shows promise for repurposing for tropical snakebite.

**Pan African Clinical Trials Registry:** PACTR202103718625048 (3/3/2021)

## Abbreviations

20WBCT      20-minute whole-blood clotting time

ALT              Alanine aminotransferase

AUC             Area under the curve

CGMRC-C   Centre for Geographic Medicine Coast

Cmax           Maximum plasma concentration

CRF             Case Report Form

CSRI           The Centre for Snakebite Research & Interventions

DMPS         2,3-bis(sulfanyl)propane-1-sulfonic acid (unithiol)

EDTA         Ethylenediaminetetraacetic acid

FBC            Full blood count

GCP            Good clinical practice

GDPR         General data protection regulation

KEMRI       Kenya Medical Research Institute

KHDSS       The Kilifi Health and Demographic Surveillance System

LSTM         Liverpool School of Tropical Medicine

SERU         Scientific and Ethics Review Unit

SPIRIT       Standard Protocol Items: Recommendations for Interventional Trials

SVMP        Snake venom metalloproteinase toxins

Tmax          Time to maximum concentration

## Introduction

### The burden of snakebite envenoming

Globally, snakebite envenoming is estimated to affect 1.8–2.7 million people, with annual mortality predicted between 80,000 and 140,000
^
1,
2
^. Despite this high mortality rate, snakebite envenoming has attracted minimal research funding, and therapeutic options have changed little over the past 50 years
^
3,
4
^.

### Snake venom metalloproteinase toxins

Snake venom metalloproteinase toxins (SVMPs) are abundant in viperid snake venoms and have an important role in causing:

Haemorrhage via hydrolysis of endothelial cell wall components including type IV collagen, hyaluronic acid, and proteoglycans.Consumption coagulopathy via the activation of blood clotting factors.Local tissue damage, which is a prominent feature of envenoming in sub-Saharan Africa.

### Limitations of antivenom

The mainstay of snakebite treatment is antivenom, which consists of polyclonal antibodies purified from immunised mammals, such as horses. Antivenom efficacy is variable and high costs have impacted on availability, particularly in sub-Saharan Africa
^
5
^.

When good quality antivenom directed against the relevant biting species is available, it has been shown to effectively reverse the consumption coagulopathy induced by SVMPs. However, few clinical trials of antivenom in sub-Saharan Africa have been conducted, and none have compared antivenom to placebo
^
6–
10
^. In Nigeria, ‘‘EchiTAb Plus-ICP’’ (ET-Plus) equine antivenom restored the 20-minute whole-blood clotting time (20WBCT) in 83% of trial participants
^
6
^. Despite access to effective antivenom, in Nigeria snakebites are estimated to contribute to 1,900 deaths and 2,400 amputations, annually
^
11
^. Unfortunately, antivenom has limited efficacy for treating venom-induced local tissue damage, probably because the onset of local tissue damage occurs before most people can access treatment
^
12,
13
^. The costs, low availability, risk of anaphylaxis and cold chain requirements of antivenom have restricted its use to secondary care settings. The risk of allergic reaction varies significantly between antivenom products. In a clinical trial conducted in Sri Lanka, the adverse reaction rate was 75%, and 43% suffered a severe adverse reaction
^
14
^.

### SVMP inhibitory action of metal chelators

In the 1950s,
*in vitro* experiments found that incubating venom with ethylenediaminetetraacetic acid (EDTA) completely inactivated its proteolytic activity
^
15,
16
^. Rabbits injected with venom that had been pre-incubated with EDTA were found to develop less necrosis
^
17
^. In 1978, the importance of zinc in the haemorrhagic and proteolytic activities of venom components was described, and it was found that removing zinc with a metal chelator (1,10-phenanthroline) inhibited these activities
^
18
^. More recently, research in mice has shown that administering CaNa
_2_EDTA inhibits haemorrhagic, proteolytic and dermonecrotic effects of
*Bothrops asper* venom
^
19
^. In mice administered with a 2.5x LD
_50_ dose of
*Echis ocellatus* venom pre-incubated with EDTA, lethality was abolished. Furthermore, EDTA outperformed heterologous antivenom in terms of mice survival and survival times
^
20
^.
*In vitro* and mouse model research has since investigated the efficacy of various metal chelators to inhibit the pathological activity of various saw-scaled viper (
*Echis* spp.) venoms
^
21
^. Of those tested, unithiol (also known as sodium D,L-2,3-dimercapto-1-propanefulfonic acid [DMPS], trade name Dimaval
^®^) showed the most promise as it is already in routine clinical use, has activity against a range of snake species, and significantly reduces envenoming associated mortality
*in vivo*
^
21
^. As well as preventing mortality, unithiol was demonstrated to effectively inhibit the formation of local haemorrhagic lesion at the site of venom delivery
^
21
^. When unithiol was co-administered with antivenom
*in vivo*, there was an additive effect with the combination treatment reducing mortality more than either product alone
^
21
^.

## Summary of existing safety data for unithiol

Safety data in humans is available for unithiol, as this drug is routinely used for the treatment of heavy metal poisoning. Unithiol is generally regarded as a safe and well tolerated therapy.

### Skin reactions

Skin reactions are the most common side effect reported for unithiol. They are invariably of low severity and of minor and short impact to the individual. The rash is reversible on stopping the medication. These reactions are usually allergic in nature and tend to increase in likelihood with subsequent doses of unithiol.

Very rarely, unithiol can cause Stevens-Johnson syndrome. There are two published cases of Stevens-Johnson syndrome occurring during treatment with unithiol
^
22,
23
^. Given that unithiol has been in clinical use for several decades and has been given to many thousands of people, the risk of this complication is regarded as extremely low. The report by Chisolm
*et al.* does not provide any clinical details
^
22
^. In the report by Van Der Linde
*et al.*, a widespread rash associated with blistering of the oral mucosa occurred in an 11-year old boy treated for mercury poisoning, with oral unithiol
^
23
^. No cutaneous epidermal detachment occurred, and the child made a complete recovery following cessation of unithiol. In these case reports, the skin reaction did not manifest until 8–14 days after commencing unithiol at a dose of 200 mg three times per day oral.

Skin reactions associated with parenteral use of unithiol have only been described at very high doses. Attempts at administering parenteral 100 mg/kg to humans were conducted in the Soviet Union in the 1960s
^
24
^. The study by Sanotskiĭ (available in Russian only), is referred to by Aposhian’s review
^
25
^, which describes necrosis and ulceration at the site of subcutaneous or intravenous injection following these doses, which are 20 times higher than the currently recommended intravenous dose. These adverse skin reactions are not described for lower doses of parenteral unithiol.

### Allergic and other immune mediated reactions

Severe allergic reactions to unithiol are extremely rare. Two cases of anaphylaxis and 21 cases of ‘hypersensitivity’ are reported in the Periodic Safety Update Report. The Dimaval
^®^ solution for injection summary of product characteristics suggests caution in administering the drug to people with allergic asthma, due to a risk of provoking an exacerbation
^
26
^. The Periodic Safety Update Report identifies 6 reports of ‘asthma’ in association with use of unithiol.

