## Study restrictions

### Dose escalation holding criteria

If any of the following scenarios occur within a group with reasonable possibility of a causal relationship with unithiol, dose escalation will be stopped pending safety review, prior to higher dose levels being evaluated. In the case a serious adverse event occurring, this will be reported in accordance with section 11.7 of this protocol, including reporting to the Sponsor and the DSMB within 48 hours.

Clinically relevant signs or symptoms or intolerable adverse events of similar nature occur in 2 or more subjects in a group that in the opinion of the Investigator warrant stopping of dose escalationOne or more subjects report a serious adverse event considered by the Investigator to be related to the study drugTwo or more severe adverse events occur which are considered by the Investigator to be related to the study drugDose escalations will only occur after a minimum period of days, depending on the dose received (as specified in
Figure 1a and
Figure 1b).

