### Solicited adverse events

Solicited adverse events are those that have been associated with unithiol and are listed in the summary of product characteristics. These are summarised in
Table 4.

**Table 4. T4:** Solicited adverse events.

Category	Solicited adverse events
Symptoms	Nausea, weakness, loss of appetite, dysgeusia (change in taste), painful injection site, abdominal pain
Physical observations	Shivering, fever, skin reactions (itching rash), Stevens-Johnson’s syndrome, hypotension (with intravenous unithiol)
Laboratory abnormalities	Leucopaenia, transaminitis, kidney injury (raised urea and creatinine)

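### Table 4 solicits no respiratory or systemic allergic event, although the protocol's own safety review links asthma, hypersensitivity and anaphylaxis to unithiol

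*Protocol article*

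**What the plan says.** The section Solicited adverse events sets the rule: "Solicited adverse events are those that have been associated with unithiol and are listed in the summary of product characteristics". Table 4 then gives the list under three categories:

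- Symptoms: "Nausea, weakness, loss of appetite, dysgeusia (change in taste), painful injection site, abdominal pain".
- Physical observations, which run from shivering to intravenous hypotension: "Shivering, fever, skin reactions (itching rash), Stevens-Johnson’s syndrome, hypotension (with intravenous unithiol".
- Laboratory abnormalities: "Leucopaenia, transaminitis, kidney injury (raised urea and creatinine".

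The section Allergic and other immune mediated reactions describes severe allergic reactions as extremely rare. From the Periodic Safety Update Report it counts 2 anaphylaxis, 21 hypersensitivity and 6 asthma reports. It adds that the product characteristics of the injection "suggests caution in administering the drug to people with allergic asthma, due to a risk of provoking an exacerbation". The Exclusion criteria bar people with asthma and give this risk as the reason.

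The section Adverse events (AEs) says that the study clinician evaluates for solicited events during admission, and that these are elicited again on days 2, 5 and 42 and at 6 months. It also says that unsolicited events are recorded to the end of the 6-month follow-up. The section Human Subjects says that participants are told about the solicited events and encouraged to come early if one occurs.

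**The concern.** The protocol treats respiratory and systemic allergic reactions as a known risk in its safety review and in its eligibility criteria, but not in the list that decides what is actively looked for. The list matters in two ways. It fixes what staff ask about at each contact, and it fixes what participants are told to watch for after discharge.

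An event outside the list is recorded if the participant mentions it or a clinician notices it. That route is usually less even than a direct question, above all for mild and short-lived symptoms. The primary objective is safety and tolerability, and the adverse-event summaries inform each dose-escalation review. If rash and nausea are asked about while wheeze and breathlessness are not, their frequencies are not measured in the same way and should not be compared as if they were.

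**Working it through.** No sample-size, power or error-rate figure bears on this point, so the check is a comparison of the protocol's sections.

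**Step 1: count what Table 4 contains.** Symptoms 6, physical observations 5, laboratory abnormalities 3; 6 + 5 + 3 = 14 items. Respiratory items: 0. Items for general hypersensitivity, angioedema or anaphylaxis: 0.

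**Step 2: set the safety review against the list.**

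| Event in the safety review | Evidence given | In Table 4? |
|---|---|---|
| Skin reactions | most common side effect, usually allergic | yes |
| Stevens-Johnson syndrome | 2 published cases | yes |
| Fall in blood pressure with rapid infusion | 2 of 5 participants in one study | yes, for intravenous dosing |
| Asthma | 6 periodic-report cases, plus the injection product-characteristics caution | no |
| Hypersensitivity | 21 periodic-report cases | only where it shows as rash |
| Anaphylaxis | 2 periodic-report cases | only in part (rash; hypotension if intravenous) |

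The last three rows give 6 + 21 + 2 = 29 reports, if no case is counted twice. The protocol gives no number exposed, so these are not rates. They show an association, not a frequency. Stevens-Johnson syndrome is listed on two published cases while asthma, with six reports, is not. The sources differ, so this comparison shows unevenness and no more.

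**Step 3: check how far the listed items stand in for the missing ones.** Itching rash captures allergy only where it reaches the skin. Hypotension is solicited only for intravenous dosing, so not in the oral cohorts, and the footnote to Table 8 says that asymptomatic hypotension is not recorded as an adverse event. Table 8 grades temperature, heart rate and blood pressure, and has no respiratory measure. No listed item would prompt a question about wheeze, breathlessness or chest tightness.

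**Step 4: check what being on the list changes.** Active elicitation at follow-up visits and advance information to participants are each stated for solicited events only. In-patient monitoring ends a minimum of 24 hours after the last dose. After the day 5 visit the next is on day 42, so between those visits detection depends on participants recognising and reporting a problem.

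**Result.** The respiratory and systemic allergic gap can be verified on the page. Its numerical effect cannot be derived from the documents.

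**The case against.** The strongest reply is that the protocol follows its own rule. The rule requires an event to be both associated with unithiol and listed in the product characteristics. The 29 reports come from the periodic safety report, and the product-characteristics statement is a caution about exacerbation in people with allergic asthma. It is not shown to be a listed adverse reaction, and those people are excluded. This stands. A reader might infer that Table 4 breaches its own rule, but the product characteristics are not at hand and no breach is shown. The point is that the rule is too narrow for the evidence the protocol itself cites. Exclusion of people with asthma lowers the expected number of events, but screening as described rests on history and examination with no lung-function test listed, so undiagnosed asthma or new bronchospasm remains possible.

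The second reply is that other safeguards exist: six months of unsolicited recording, in-patient dosing, scheduled physical examinations and vital signs, and blood-pressure monitoring around infusions. This also stands. It makes it unlikely that a serious acute reaction would be missed, and leaves mild or later events as the exposed group.

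Three stronger readings are tempting but not supported:

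- *Injection-site damage is also left out.* Pain at the injection site is solicited. The safety review "describes necrosis and ulceration at the site of subcutaneous or intravenous injection following these doses", but those doses were 100 mg/kg, and the protocol says such reactions are not described at lower parenteral doses. The trial's maximum intravenous dose is 10 mg/kg, and 100 / 10 = 10.
- *The loss is greatest in the multiple-dose cohorts.* The statement that reactions become likelier with subsequent doses concerns skin reactions, which are solicited.
- *Holding rules would fail to trigger.* One criterion is that "Clinically relevant signs or symptoms or intolerable adverse events of similar nature occur in 2 or more subjects in a group", but it also needs the investigator's opinion that stopping is warranted. A single related serious event, or two related severe events, triggers a hold regardless, and the investigators or the local safety monitor can refer any lesser event to the data safety monitoring board.

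**Conclusion.** The point holds in a limited form. Table 4 has no respiratory or systemic allergic item, although the protocol's own safety review links such events to unithiol and its exclusion criteria act on the asthma risk. Mild wheeze, breathlessness and non-cutaneous hypersensitivity would be captured only as unsolicited events, and so less consistently than rash or nausea.

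This rests on one assumption: that asking directly finds more mild events than waiting for a report. No percentage loss should be attached to it. The documents give neither a true rate of these reactions nor a capture rate for either route, and the protocol calls severe allergic reactions extremely rare. The expected number of affected records is therefore probably small. Priority is low to moderate: a cheap gain in ascertainment of the primary outcome, not a flaw that undermines the trial.

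**What to change.** Reconcile the section Allergic and other immune mediated reactions with the section Solicited adverse events. Extend the rule so that solicited events are those associated with unithiol in the product characteristics, the Periodic Safety Update Report or the protocol's own safety review.

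Then add to Table 4:

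- under symptoms: wheeze, breathlessness or chest tightness;
- under physical observations: bronchospasm, angioedema or other hypersensitivity, including anaphylaxis.

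Carry the same items into the case report form checklist and into what participants are told to watch for. If cohorts have already been dosed when the change is made, report which cohorts were assessed under each list, so that a rise in recorded events is not mistaken for a dose effect.

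The cost is a few lines on forms used at contacts already scheduled, plus the approval step for the change. No dose, visit or holding rule changes. The downside is that slightly more background respiratory illness will be recorded; the existing causality categories in Table 6 can be used to classify it.

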### Cardiovascular effects

Rapid infusion of unithiol solution via the intravenous route has been associated with transient asymptomatic hypotension in a single published article. In a previous pharmacokinetic study of unithiol, two of five participants developed transient falls in systolic blood pressure, of 20 mmHg
^
27
^. These episodes were not associated with any symptoms, any change in heart rate, or any fall in diastolic blood pressure. Unithiol is not cardiotoxic and is not associated with any cases of clinically significant cardiac arrhythmia.

### Mineral deficiency

Although the mechanism of action of unithiol would suggest that mineral deficiency would be an expected side effect (such as magnesium or zinc deficiency), this is not borne-out in published or post-marketing data. Data from Periodic Safety Update Reports have identified only a single case defined as ‘non-serious decreased electrolytes.’ No published reports of clinically significant mineral deficiency were identified.

### Renal effects

Unithiol is not nephrotoxic.

### Liver effects

Unithiol is not hepatotoxic.

### Effects of higher doses of unithiol

Animal toxicity data have suggested that high doses of unithiol can be tolerated. In rats, 150 mg/kg administered orally 5 times per week for 63-weeks was tolerated with no observable effects
^
28
^. In beagles, 45 mg/kg administered orally for 6-months was tolerated with no observable effects
^
29
^. When a dose of 75 mg/kg was administered intravenously twice daily to beagles, anaemia as well as reduced iron content in the liver and spleen was noted
^
29
^. In rabbits receiving 500 mg/kg administered orally twice daily for 6–10 days, no clinical events or changes in blood parameters were noted
^
30
^.

Published reports have also described giving high doses of unithiol to humans. Very high doses of parenteral unithiol (100 mg/kg) were given to people in the report by Sanotskiĭ in the 1960s (available in Russian only)
^
24
^. This study is referred to in Aposhian’s review
^
25
^, which describes necrosis and ulceration at the site of subcutaneous or intravenous injection. No other adverse events were described, although it is unclear if formal follow-up and adverse event reporting were followed.

The Dimaval
^®^ product monograph includes a report of the accidental administration of 100 mg/kg parenterally
^
30
^. Skin necrosis at the injection site occurred, but no other morbidity was highlighted
^
30
^.

In a study by Stantschew
*et al.* in 1974 (article in German), 216 adult workers with chronic mercury exposure were administered unithiol 1,000 mg intramuscularly. No adverse events were reported
^
31
^.

In a case report by Heinrich-Ramm
*et al.*, a 21-year male with arsenic over-dose was administered the following regimen of unithiol:

250 mg/hour intravenous for 1 day125 mg/hour intravenously on day 262.5 mg/hour intravenously on days 3–5

The total dose of unithiol received was 15.2 grams. A mild increase in transaminases were reported, but the patient was otherwise well and made a good recovery from the arsenic poisoning
^
32
^. It is uncertain whether the transaminase rise was due to arsenic poisoning or unithiol.

## Summary of existing pharmacokinetic data for unithiol

In total, four studies on unithiol pharmacokinetics have been conducted by a research group at The University of Arizona. Key finding from these studies are summarised in
Table 1.

**Table 1. T1:** Summary of published human pharmacokinetic data.

Paper	Participants	Dose of unithiol	Main findings
Maiorino 1991 ^ 33 ^	10 male volunteers, aged 24”34 years, weighing 68”98 kg	300mg oral single dose	Absorbed unithiol is rapidly metabolised to disulphide forms. Cmax 11.9 µM, Tmax 3.7 hours, AUC 148 µM hours, half-life 9.1 hours (For total unithiol).
Hurlbut 1994 ^ 27 ^	5 volunteers (4 male, 1 female), aged 24 to 32 years, weighing 49”93 kg	3 mg/kg intravenous single dose	Unithiol is rapidly transformed to disulphide forms (>80% within 15 minutes). Excretion is mostly in urine in disulphide form. Elimination half-life 1.8 hours for parent drug; 20 hours for total unithiol.
Maiorino 1996 ^ 34 ^	4 male volunteers, aged 23 to 27 years, weighing 86”91 kg	300mg oral single dose	Majority of circulating unithiol (>60%) is plasma protein bound. Remaining drug is predominantly in disulphide form (>30%); remainder is unbound parent drug (<1%). Binds to albumin via disulphide complex. Majority of excreted drug is altered and in a disulphide form. Protein bound unithiol theorised to act as a reservoir of the drug and may prolong its activity.
Maiorino 1996 ^ 35 ^	11 factory workers with occupational mercury exposure (7 male and 4 female), mean age 34 years.	300 mg oral single dose	Identified increased mercury excretion and propose using unithiol as a challenge test for identifying mercury poisoning – this approach has since been discredited. Not relevant to present study.

AUC, area under the curve; Cmax, maximum plasma concentration; Tmax, time to maximum concentration.

